## Abstract

**Background:**

Cervical radiculopathy is a common form of neck pain and has been shown to lead to severe disability. Clinical rehabilitation approaches for cervical radiculopathies commonly include exercise and manual therapy interventions targeting the opening of intervertebral foramen, but evidence regarding their effectiveness is scarce. The primary objective of this randomised clinical trial is to compare, in terms of pain and disability, a rehabilitation program targeting the opening of intervertebral foramen to a conventional rehabilitation program, for patients presenting acute or subacute cervical radiculopathies. The hypothesis is that the rehabilitation program targeting the opening of intervertebral foramen will be significantly more effective in reducing pain and disability than the conventional rehabilitation program.

**Methods/Design:**

This study is a double-blind (participants and evaluators blinded) randomised clinical trial that will allow the comparison of patients with a cervical radiculopathy randomly assigned to one of two groups: one group will receive a 4-week rehabilitation program targeting the opening of intervertebral foramen, and the second group will receive a 4-week conventional rehabilitation program. Thirty-six subjects with cervical radiculopathy will be recruited from participating medical and physiotherapy clinics and will be evaluated at baseline, at the end of the 4-week program and four weeks following the end of the program. The primary outcome measure will be the validated Neck Disability Index questionnaire. Secondary outcome measures will include the short version of the Disabilities of the Arm, Shoulder and Hand questionnaire, a numerical pain rating scale, cervicothoracic mobility and patients' perceived global rating of change. During the 4-week rehabilitation program, each participant will take part in eight physiotherapy treatment sessions (2 session/week) and will perform a home exercise program. A mixed-model, 2-way ANOVA will be used to analyze the effects of the rehabilitation programs.

**Discussion:**

Control trials are needed to define ideal intervention approaches in rehabilitation for this population. This randomised clinical trial will be the first study that directly compares a rehabilitation program targeting the opening of intervertebral foramen to a conventional rehabilitation program for patients with cervical radiculopathy. The results of this study may help to establish best clinical practice guidelines for this patient population.

**Trial Registration:**

ClinicalTrials.gov: NCT01500044

## Background

Cervical or neck pain is a general term used to designate any musculoskeletal disorder in the cervical region. Various pathologies encompass that generic definition and are most commonly related to degenerative changes or inflammation of cervical structures such as intervertebral discs, articular facets joints or nerve roots. Neck pain is a very common, disabling and costly condition [1-3]. According to a review by the Neck Pain Task Force pertaining the prevalence of neck pain in industrialised countries, annual prevalence is situated within 30 to 50% in adult populations [1]. In accordance with these results, in Canada, a bi-annual prevalence of 54% has been reported [1].

Cervical radiculopathy forms an important subgroup of neck disorders and, although less prevalent than general neck pain, it has been shown to lead to more severe pain and disability [4-9]. Cervical radiculopathy primarily results from an inflammation of a cervical nerve root induced by a lesion reducing the intervertebral foramen [10]. This reduction is primarily induced by a herniated disc or a degenerative lesion of zygapophysial joints [11-13]. Typical symptoms of cervical radiculopathy include pain in the cervical or periscapular region and in the upper limb, as well as neurological signs such as paresthesia, numbness, weakness and loss of reflexes in the affected nerve root distribution [14].

The diagnosis of cervical radiculopathy is commonly made through patient history and physical examination. Wainner et al. have shown that a positive response to the following four clinical tests results in a high predictive value for a diagnosis of cervical radiculopathy [15]: 1- cervical distraction test, 2- upper limb tension test (ULTT), 3- Spurling test, and 4- ipsilateral cervical rotation reduced by more than 60°. If all four of these tests are positive, the positive likelihood ratio (LR+) of having a cervical radiculopathy is 30. If three out of these four tests are positive, the LR+ decreases to 6. According to Straus et al., a LR+ superior to 10 is considered large, and between 5 and 10 moderate; thus, it increases the possibility that the impairment in question is present [16]. Hence, by combining these clinical tests, the possibility of obtaining a good clinical diagnostic accuracy in patients presenting signs and symptoms compatible with cervical radiculopathy is high.

While the clinical diagnostic process of cervical radiculopathies is relatively well documented, studies evaluating the effectiveness of rehabilitation interventions remain sparse [17-20]. Published in 2010, a systematic review by Miller et al., pertaining to the effects of manual therapy and exercises on the treatment of neck pain, concluded that there is little evidence supporting the efficacy of these modalities in the treatment of cervical radiculopathies [17]. Of the 17 randomised clinical trials (RCT) included in this systematic review, only three included subjects who presented radicular signs. Furthermore, in these three RCTs, subjects with or without radicular signs were combined for the statistical analysis used to evaluate the effects of the intervention. The authors of the systematic review concluded that, for neck pain, a combination of cervicothoracic mobilisations and exercises is the most effective rehabilitation approach to reduce pain and disability [17]. No specific recommendation was, however, brought forth for cervical radiculopathies. Three RCTs published in 2009, but not included in the systematic review by Miller et al., also evaluated the effects of rehabilitation approaches for the treatment of cervical radiculopathy [21-23]. Kuijper et al. randomised 205 patients suffering from cervical radiculopathy within 3 groups: a "*cervical collar*" approach, an "*active physiotherapy*" approach, and a "*wait and see*" approach [21]. The "*active physiotherapy*" approach involved mobilisations and stabilisation exercises; whereas the "*cervical collar*" approach included the use of a semi-hard cervical collar worn at all times for three weeks, then gradually weaned for three additional weeks. Three and six weeks into the intervention, a diminution of arm and neck pain was observed in the "*cervical collar*" and "*active physiotherapy*" groups. Functional improvement was also observed in both experimental groups at three weeks, but was only noted in the "*cervical collar*" group at six weeks. While this study's conclusions seem to favour the "*cervical collar*" approach, it remains a controversial treatment option. According to the Quebec Task Force, cervical collar should be avoided due to its passive and decondition properties, and because it has been shown to hinder neck pain recuperation following motor vehicle accidents [24]. These initial recommendations regarding the potential drawbacks of cervical collar use have recently been generalised to encompass all types of neck pain [19,25]. Finally, two other studies have evaluated the effect of intermittent tractions on patients suffering from cervical radiculopathy [22,23]. They have, however, obtained contradictory results: one demonstrated that the addition of tractions to a conventional intervention does not increase treatment efficacy [22], whereas the other claimed that tractions supplementing a conventional intervention improves cervical and radicular pain, in comparison to a conventional intervention [23].

Numerous other approaches are commonly utilised in clinical settings, but a formal demonstration of their efficacy remains to be shown. Clinical approaches for cervical radiculopathies commonly include interventions targeting the opening of intervertebral foramen [26]. It is well recognised that cervical movements causing the opening of intervertebral foramen, such as flexion, rotation and lateral flexion contralateral to the nerve root, increase the volume of the foramen, and consequently might decompress a swollen nerve root [27-31]. Inversely, movements of extension, rotation and lateral flexion ipsilateral to the nerve root close the intervertebral foramen around the root. Thus, for acute and sub-acute radiculopathies, intervention programs should include treatment modalities that allow the opening of the intervertebral foramen. On the other hand, movements and positions that lead to intervertebral foramen closure should be avoided. However, no studies have evaluated the effects of a treatment approach that specifically take into consideration these biomechanical principles. Due to the important incapacities related to cervical radiculopathy, and to the few studies pertaining to the efficacy of rehabilitation in this population, we believe in the importance of better understanding the potential of cervical mobilisations and exercises that lead to the opening of the intervertebral foramen. The primary objective of this RCT is to compare, in terms of pain and disability, a rehabilitation program targeting the opening of intervertebral foramen to a conventional rehabilitation program, in patients presenting acute or subacute cervical radiculopathies. Based on biomechanical principles, our hypothesis is that the rehabilitation program targeting the opening of intervertebral foramen will be significantly more effective in reducing pain and disability than the conventional rehabilitation program, mainly at the 4-week evaluation. In considering the passage of time, the differences between the two interventions should be less important at 8-week.

## Methods/Design

### Study Design

This double-blind randomised clinical trial will allow the comparison, in terms of pain and disability, of patients presenting a cervical radiculopathy which will have been randomly assigned to one of the two intervention groups: the first group (n = 18) will receive a 4-week rehabilitation program targeting the opening of intervertebral foramen, the second group (n = 18) will receive a 4-week conventional rehabilitation program. Participants will be evaluated on three separate occasions: at baseline (week 0), at the end of the 4-week program (week 4), and four weeks following the end of the program (week 8).

### Participants

Thirty-six subjects with cervical radiculopathy will be recruited from participating medical and physiotherapy clinics in the Quebec City (Canada) area. The study will include patients who meet the following inclusion criteria: 1- age greater than 18 years and less than 65 years; 2- pain, paresthesia or numbness in the upper-limb with cervical or periscapular pain for less than 3 months; 3- at least one neurological sign (dermatomes, myotomes or reflexes) of an inferior motoneuron lesion to the upper-limb; and 4- positive responses to at least 3 of the 4 following clinical tests: Spurling Test, Upper Limb Tension Test, Cervical Distraction Test, and less than 60° of cervical rotation on the impaired side. The following exclusion criteria will be used for this study: 1- prior surgery to the cervicothoracic spine; 2- bilateral upper-limb symptoms; 3- signs of superior motoneuron impairments (bilateral paresthesia, hyperreflexia, spasticity); 4- cervical spine injection in the previous four weeks; 5- current use of steroidal anti-inflammatory drugs; and 6- financial compensation for the cervical condition. Before the beginning of the study, physiotherapists and physicians from participating clinics will be contacted to explain the goals of the study and eligibility criteria. Patients presenting pain, paresthesia or numbness of the upper limb with or without cervical pain will be identified from the participating clinics. The treating physiotherapist or physician will explain the goal of the study to the identified patients to enquire about their interest in participating to the study. Those interested will be contacted by phone by a member of the research team for a preliminary screening of their condition (sociodemographic, symptomatology, medication criteria). If they meet the eligibility criteria, and after providing written informed consent, they will be evaluated by an independent physiotherapist, at the Center for Interdisciplinary Research in Rehabilitation and Social Integration (CIRRIS), who will perform physical tests to determine their full eligibility. Demographic data (gender and age) of patients who refuse to participate and of ineligible patients willing to participate will be collected to evaluate potential selection bias. The Institutional Review Board at Quebec Rehabilitation Institute has granted approval for the study.

### Examination procedure and randomisation

After recruitment, the eligible participants will take part in the baseline evaluation. They will complete a questionnaire on sociodemographic, symptomatology and comorbidity, and three self-reported questionnaires on pain and disability: the Neck Disability Index (NDI), the short version of the Disabilities of the Arm, Shoulder and Hand Questionnaire (*Quick*DASH), and a numerical pain rating scale (NPRS). Finally, they will undergo a physical examination of the cervicothoracic spine, which will include the evaluation of cervicothoracic range of motion using a CROM (cervical inclinometers).

After baseline evaluations, assignation of patients to either the conventional or experimental intervention will be performed. To reduce contamination bias, the two programs will be given in different clinics. An independent research assistant will open the randomisation envelope indicating the participant's assignment to the group of clinics that corresponds to the experimental or control group. The research assistant will be blind to the baseline evaluation results and to the assignation of which clinic is providing which intervention. The research assistant will give the list of the clinics providing the rehabilitation program assigned to the participant, and the participant will choose the clinic of their choice. Random number generator will be used to establish randomisation lists prior to the initiation of the study. A member of the research team not involved with data collection will generate the randomisation list. To make sure that two equal groups of 18 subjects will be obtained, blocked randomisation will be used (block size of 6). Three physical therapy clinics will provide the control rehabilitation program and three different clinics the experimental rehabilitation program.

At the end of the 4-week rehabilitation program (maximum 3 days after the last treatment session), and four weeks after the end of the program, the three self-reported questionnaires (NDI, *Quick*DASH, and NPRS), as well as cervicothoracic range of motion will be revaluated. Furthermore, at the two follow-up evaluation sessions, a question pertaining to global change since the initial session (*Global rating of Change *[GRC]) will be completed. An independent physiotherapist, blind to the group assignment, will perform the evaluations according to standardised procedures.

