### Rehabilitation Programs (independent variables)

Physiotherapists working in six physiotherapy clinics in the Quebec City area will provide the rehabilitation programs. Each participant will receive eight physiotherapy treatment sessions during a 4-week span (2 sessions/week; 30 to 45 minutes each session) and will perform a home exercise program. At the beginning of each session, the physiotherapist will conduct a standardised biomechanical examination of the cervicothoracic spine. It will consist of an intervertebral segmental mobility evaluation using lateral glides at the cervical spine and postero-anterior glides at the thoracic spine (T1 to T6). Segmental mobility will be rated as normal, hypomobile or hypermobile. Sandmark & Nisell and Rey-Eiriz et al. demonstrated that this rating of cervicothoracic mobility is sensitive (> 0.80) and specific (> 0.70) [44,45]. Furthermore, this evaluation of segmental mobility is recommended in the *Neck Pain Clinical Practice Guide *of the *American Physical Therapist Association *[5]. The results of the biomechanical examination, as well as the nature and intensity of the intervention, will be documented using standardised forms.

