### Sample size and Analyses

The sample size calculation is based on the primary outcome measure, the NDI. The NDI has a clinically important difference of 7/50 (14/100) points for patients presenting a cervical radiculopathy. The standard deviation reported in the literature for this population is 18.4 [33]. The considered parameters are 0,05 for type I error (α) with a power of 0,80 (1-β). For an analysis of variance (ANOVA), the sample size required is 16 subjects per group. However, 18 subjects per group will be recruited to compensate for withdrawals and probable loss of follow-up. This sample size will provide sufficient power to detect a clinically important difference between the two groups.

Descriptive statistics (mean, standard deviation, median frequency counts) will be calculated for all outcome measures at the different times of measurement (week 0, 4 and 8) to summarise results. Baseline demographic data will be compared (independent Student t-tests and Chi-squared tests) across groups to establish the comparability of covariables. If needed, statistical adjustments will be made for baseline characteristics that are significantly different between groups. All data will be tested to ensure they meet the assumptions for the inferential statistical analyses. If they do not meet the necessary assumptions, appropriate non-parametric procedures will be used. An intention-to-treat analysis will be used in which all participants will be analysed in the group to which they were originally assigned. All dropouts and the reason for dropping out of the study will be reported. Any harms or unintended effects during the rehabilitation programs will be recorded, reported and discussed.

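### The clinic is chosen after the allocation envelope is opened, so refusal or delay over access to the assigned arm's clinics falls after randomisation and could differ between arms

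*Protocol article*

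**What the plan says.** All of this is in the protocol article.

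- **Recruitment and screening (Participants).** Patients come through clinics: "The treating physiotherapist or physician will explain the goal of the study to the identified patients". A telephone call then gives a "preliminary screening of their condition (sociodemographic, symptomatology, medication criteria", followed by written consent and physical tests for full eligibility.
- **Order of allocation (Examination procedure and randomisation).** "After baseline evaluations, assignation of patients to either the conventional or experimental intervention will be performed". Next, "An independent research assistant will open the randomisation envelope indicating the participant's assignment to the group of clinics" for the experimental or control program. The assistant then hands over "the list of the clinics providing the rehabilitation program assigned to the participant, and the participant will choose the clinic of their choice".
- **Separate clinics (same section).** "Three physical therapy clinics will provide the control rehabilitation program and three different clinics the experimental rehabilitation program".
- **Attendance (Rehabilitation Programs).** "Each participant will receive eight physiotherapy treatment sessions during a 4-week span (2 sessions/week; 30 to 45 minutes each session".
- **Analysis (Sample size and Analyses).** "An intention-to-treat analysis will be used in which all participants will be analysed in the group to which they were originally assigned". Dropouts are to be reported with reasons. The stated requirement is 16 per group, with 18 recruited to cover withdrawals and losses.
- **Assessment (Blinding; Outcome measures).** All evaluations take place at the research centre (CIRRIS), outside the treating clinics.

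**The concern.** The clinic sets do not overlap, so the allocation decides where the patient must go twice a week for four weeks. On the described order, a patient who finds no workable clinic on the assigned list discovers this only once already randomised. Had the same patient been allocated to the other set, the problem might not have arisen. That is what ties a refusal, or a delay in starting, to the arm.

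Two things are at stake. The first is the meaning of the comparison: people who receive neither program are counted in one arm or, if they also stop attending evaluations, are missing from it for an arm-related reason. The second is timing. The first follow-up is anchored to the final treatment session (within three days of it). A non-starter has no such session, and a late starter is assessed longer after baseline. The Background itself expects the passage of time to narrow the difference between programs.

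**Working it through.** **1. The sequence.** Put in order, the article gives: telephone screen of the condition; consent; physical eligibility tests; baseline evaluation; envelope; the assigned arm's list; choice of clinic. No step before the envelope concerns clinic access. Every step that does comes after it and involves one arm's clinics only.

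**2. The allowance for loss.** The plan recruits 18 and requires 16, so the margin is 18 − 16 = 2 per arm, or 2/18 = 11.1%. One patient is 1/18 = 5.6% of an arm. Three unassessed non-starters in one arm (3/18 = 16.7%) would exceed that arm's margin before any ordinary dropout.

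The figure of 16 does not itself follow from the stated inputs. With a difference of 14/100, SD 18.4 (taken to be on the 0–100 scale), two-sided 5% and 80% power, n = 2 × (1.96 + 0.84)² × (18.4/14)² ≈ 27.1, so 28 per group. That is a separate matter, and the present point does not rest on it.

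**3. Non-starters who are not assessed: effect on power.** Two-sided t-test power with 18 in one arm and an assumed number in the other:

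| Patients in the other arm | SD 18.4 | SD about 13.7 (at which 16 per group gives 80%) |
|---|---|---|
| 18 | 0.60 | 0.85 |
| 16 | 0.57 | 0.82 |
| 15 | 0.56 | 0.81 |
| 13 | 0.52 | 0.78 |

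The power cost of a few losses in one arm is small. The harm is that the losses would be related to the arm.

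**4. Non-starters who are assessed: effect on the contrast.** Let D be the true NDI difference between programs, k the number of non-starters out of 18 in an arm, and u the points by which a non-starter ends up worse than a conventional-program patient. Suppose non-starters are otherwise like the rest.

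- All in the experimental arm: observed difference = D − (k/18)(D + u)
- All in the control arm: observed difference = D + (k/18)u
- k in each arm: observed difference = D(1 − k/18)

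Take D = 7 (the stated clinically important difference on the 0–50 scale), k = 3 (assumed), and u from 0 to 7 (assumed range):

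| Where the three are | u = 0 | u = 7 |
|---|---|---|
| Experimental arm | 7 − 7/6 = 5.83 | 7 − 14/6 = 4.67 |
| Control arm | 7.00 | 7 + 7/6 = 8.17 |
| Three in each arm | 5.83 | 5.83 |

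The same number of non-starters can shrink the observed difference, leave it alone or enlarge it. Only equal non-starting in the two arms gives simple dilution whatever the value of u.

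**The case against.** The strongest reply is that the consequence is possible but not shown. The article gives no clinic locations, no travel distances and no expected number of refusals. All six clinics are in the same city area from which patients are recruited, and a choice among three already eases access. Nothing says that the two sets differ in accessibility. Nor does it say that the recruiting clinics are the treating clinics, so the idea of patients being steered away from their own physiotherapist is conjecture. Participants are meant to be blind to the program, so a refusal would reflect the clinic and not a treatment preference. Non-starters stay in their assigned arm for analysis, reasons for dropout are reported, and evaluation does not depend on attending a treating clinic. Finally, the article does not say what patients were told about treatment sites at the telephone call or at consent.

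Most of this stands, and it limits the size of the point. It does not remove it. The stated order still puts the only described encounter with the clinics after the envelope, and the sets are still distinct by arm. Intention-to-treat keeps a non-starter in the analysis but cannot give that patient a program, and off-site assessment helps only if the patient attends.

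A reader might infer that non-starting will be common, will differ between arms, or will always dilute the effect, for example to 5.8 points. The documents do not support this. No rate is given, and 5.8 requires particular assumed cases: three non-starters in the experimental arm alone, all assessed and doing as well as conventional-program patients, or three assessed non-starters in each arm.

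**Conclusion.** The point holds as a weakness in the order of steps. Refusal or delay over clinic access would fall after randomisation, is tied to the arm's set of clinics, and could therefore differ between arms. Its size is unknown and its direction depends on the arm. The only firm figure is the margin: more than two unassessed patients in an arm exceed the allowance of 18 against 16. The shifts in the NDI difference (from 4.67 to 8.17 around a true 7) illustrate three assumed non-starters and an assumed range for u; they are not predictions.

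The conclusion assumes that patients are not asked about the clinics before the envelope, which is read from the described order and not expressly stated. It would be wrong to go further and say that comparability is lost. That would follow only if non-starters also missed evaluation, and nothing in the article shows that they would. The point is worth acting on because the source of trouble is avoidable at little cost, and an analysis plan cannot move the choice ahead of randomisation afterwards.

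**What to change.** In Examination procedure and randomisation, insert a step between baseline evaluation and the envelope:

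- Show the patient one ungrouped list of all six clinics and record every clinic they agree to attend twice a week for four weeks.
- Randomise only patients who accept at least one clinic in each set.
- After the envelope is opened, book an accepted clinic from the assigned set.

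The list should not be split into two labelled groups, because that would show participants how the arms are formed and could weaken their blinding. The research assistant applies the grouping and stays blind to which set gives which program. If clinic access is already settled earlier, for instance at consent, the section should say so.

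The cost is one entry on the baseline form. A few patients who cannot attend one of the sets will not be randomised, which slightly slows recruitment to a 36-patient trial. The article already plans to collect age and gender for ineligible patients willing to take part, so this group can be described.

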### Blinding

A double-blind design will be used, in which the participants and evaluators will be blinded. Due to the nature of the intervention, it is not possible to blind the treatment provider to the treatment given. However, we think that the participants can be blinded since they will not be aware of the precise type of mobilisations received and to reduce potential contamination bias, the two programs will be given in different clinics. To evaluate the effectiveness of the blinding, the participants and the evaluator will complete a questionnaire related to their opinion of the allocation at the week-4 follow-up evaluation. We will blind the evaluator performing the outcome evaluations and the evaluation session will take place outside the treating clinics. The evaluator and treatment providers will be different physiotherapists. Patients will be instructed not to discuss the specific mobilisation techniques and exercises received with the evaluator. At the end of study, participants will be informed of their group allocation.

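### A single stated block size of 6 makes an expected 9 of 36 assignments certain to an observer of the full sequence; varied, undisclosed blocks are a nearly free improvement (minor)

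*Protocol article*

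**What the plan says.** The allocation rule is in the Protocol article, *Examination procedure and randomisation*: "To make sure that two equal groups of 18 subjects will be obtained, blocked randomisation will be used (block size of 6". No other block size is mentioned. The only reason given for blocking is equal group sizes.

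Two features make past assignments visible. The same section states: "Three physical therapy clinics will provide the control rehabilitation program and three different clinics the experimental rehabilitation program". *Blinding* adds that "it is not possible to blind the treatment provider to the treatment given".

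The safeguards are in the same sections:
- An independent research assistant opens the envelopes. This person is blind to baseline results and to which clinics deliver which program.
- Assignment follows consent, eligibility testing and the baseline evaluation.
- The evaluator is blinded and works away from the treating clinics.
- On the list itself: "A member of the research team not involved with data collection will generate the randomisation list".

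Entry to the trial begins earlier. Under *Participants*, treating physiotherapists and physicians identify patients, and then: "Those interested will be contacted by phone by a member of the research team for a preliminary screening of their condition". *Participants* also provides for recording the age and gender of refusers and of willing but ineligible patients, so that selection bias can be examined.

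**The concern.** In a block of 6 with three places per arm, once one arm has used its three places the rest of the block is known. If the size never changes, anyone who has followed the sequence knows when this has happened. Here the arm is readable from the clinic a participant attends, so past assignments are easier to learn than in a trial whose arms share clinics.

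Someone who can foresee the next assignment, and who also influences referral, screening or the timing of entry, could bring a patient forward or hold one back. With 18 per group and a self-reported primary outcome, a few steered entries could matter, and an intention-to-treat analysis cannot undo selection that took place before assignment. The stated purpose, two groups of 18, does not require a constant block size.

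**Working it through.** **Inputs.** Total 36 (*Participants*: "Thirty-six subjects with cervical radiculopathy will be recruited from participating medical and physiotherapy clinics"). Eighteen per group (*Study Design*: "the first group (n = 18) will receive a 4-week rehabilitation program targeting the opening of intervertebral foramen", with the same number in the other group). Block size 6, so 3 per arm in each block.

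**The plan's own figure.** 36 / 6 = 6 complete blocks, and 6 × 3 = 18 per arm. The stated purpose is met exactly.

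**Certain assignments with fixed blocks of 6.** There are C(6,3) = 20 equally likely blocks. An assignment is certain if one arm's three places are already used.
- 1st to 3rd: never.
- 4th: the first three must be the same arm, 2/20 = 1/10.
- 5th: the last two must be the same arm, 8/20 = 2/5.
- 6th: always, 1.

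The sum is 0.1 + 0.4 + 1 = 1.5 per block. The closed form 2m/(m+1) with m = 3 per arm gives 6/4 = 1.5. Counting blocks agrees: 12 have one certain assignment, 6 have two and 2 have three, so (12 + 12 + 6)/20 = 1.5. Over six blocks this is 6 × 1.5 = 9 of 36, or 25%.

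**Best-guess success.** Always guessing the arm that is behind is right in m + (4^m / C(2m,m) − 1)/2 cases per block. With m = 3: 3 + (64/20 − 1)/2 = 4.1 of 6, or 68.3%, against 50% with no information.

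**Alternatives that keep 18:18.** The observer again sees every earlier assignment. For the varied blocks, the observer knows which sizes are used but not their order.

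| Scheme | Certain, of 36 | Best guess right |
|---|---|---|
| Six fixed blocks of 6 | 9.0 (25%) | 68.3% |
| Blocks 4, 4, 6, 6, 8, 8 in random order | about 2.4 (7%) | about 68% |
| One random 18:18 permutation | 1.9 (5%) | about 59% |

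The varied sizes total 2 × (4 + 6 + 8) = 36, with 2 × (2 + 3 + 4) = 18 per arm. Their row comes from simulation (runs of 1,000 and 3,000 lists). The last row uses the two formulas with m = 18: 36/19 = 1.9 certain, 59.1% guessed correctly.

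**Who has the full view.** From the text, two people.
- The envelope-opener sees the sequence of clinic groups, but is told neither the baseline results nor which program each group gives.
- The list-maker knows every assignment whatever the block size, so varying the blocks changes nothing for that person.

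A provider sees one clinic of six. If participants choose equally among the three clinics offered (an assumption; the article gives no figures), a given clinic averages 36/6 = 6 patients, one per block. It receives all three of its arm's patients in a given block with probability (1/3)³ = 1/27. The chance that some one of that arm's three clinics does so is 3 × 1/27 = 1/9. Even then the provider is not shown the block boundaries.

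**The case against.** The strongest reply is that the observer behind the 25% may not exist among those who could act on it. The envelope-opener is independent, doubly blinded and acts after baseline evaluation, with no stated part in screening. Providers see fragments. Printing the block size in an article does not show that recruiting staff were told it. Varying the sizes also leaves best-guess success where it was. Most of this stands: it limits the severity and means that 25% must not be quoted without its condition. It does not show that the constant size serves any purpose, and assigning after baseline does not stop a prediction made before the next patient is referred or screened.

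A reader might infer three stronger points, none of which the documents support.
- **That about a quarter of assignments are foreseeable by trial staff.** The text gives no referrer, screener or provider the complete ordered sequence.
- **That the list-maker may also screen or enrol.** The article bars this person from data collection and is silent on the rest. Phone screening gathers personal and symptom information and can fairly be read as data collection. Fuller separation of roles is detail that a condensed article commonly leaves to the full protocol.
- **That the block size undermines the evaluator's blind.** Working out the rest of a block requires the evaluator already to have learned the arms of three same-arm patients in it, and its boundaries. That is a prior failure of blinding, which the plan guards against by off-site evaluation, separate staff and instructions to patients, and checks by questionnaire.

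**Conclusion.** The point holds as a minor, inexpensive improvement. The article fixes and states one block size where the clinic reveals the arm and providers are unblinded. Under that rule an expected 9 of 36 assignments (25%) are certain, on two assumptions: the observer has seen all earlier assignments in order, and knows where each block starts. For anyone with a partial view the number is smaller, and the article does not allow it to be computed. The safeguards lower the remaining risk at referral and screening without closing it. Varied blocks remove most of the certain predictions (9 down to about 2.4) but not the advantage of an informed guess, which stays near 68%. Nothing in the passage is contradictory or miscalculated, and nothing shows that allocation was in fact predicted.

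**What to change.** In *Examination procedure and randomisation*, replace the single block size with randomly ordered blocks of varying size, and state that the sizes are withheld from those who refer, screen, enrol or evaluate. Two blocks each of 4, 6 and 8 would serve: they total 36 and keep 18 per group. The figure of about 2.4 already allows for an observer who knows the sizes but not their order.

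The cost is one run of the random number generator already planned and a sentence of text, with the same envelopes and staff. The downside is slightly looser balance between groups over calendar time, or if recruitment stops early. A single random 18:18 permutation would also lower best-guess success, to about 59%, but gives up more of that balance; varied blocks are the more moderate change.
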